Research on recovery shows that 38 and 78% of patients with PDOC due to traumatic brain injury (TBI) regain (minimal) consciousness at respectively 3 and 12 months post injury [2]. In patients with non-traumatic brain injury (NTBI) only 17% regains consciousness at 8 months post injury [2]. Aidinoff et al. [14] demonstrated an improvement in survival and recovery of consciousness in UWS patients over the last two decades after EIN, and similar outcomes for both TBI and NTBI UWS. These outcomes suggest that improvements in acute medical care and EIN have contributed to advances in UWS care. Treatment started within 8 weeks after injury is associated with better outcomes in terms of LOC and functioning, gained in a faster pace than treatment started after 8 weeks [15–17]. In patients with PDOC of mixed aetiology with a mean time follow-up of 5 years, 40% of survivors reached functional independence, while 42% of patients able to respond to a self-report questionnaire, reported a poor quality of life [18]. The EIN programme in the Netherlands has been studied before; in patients aged < 25 years recovery of consciousness occurred in two-thirds at the end of the EIN programme [19] and two-thirds of the patients who were fully conscious at discharge were able to live independently after 10–12 years [20].

Prognostic factors associated with better recovery from PDOC are younger age at onset, traumatic aetiology, less severe comorbidities and less severe neurological impairment, i.e. higher level of consciousness at admission to EIN [2, 4, 15, 21–25]. However, most studies on recovery after PDOC suffer from methodological issues, such as a retrospective design [2] and variability in clinical decision making in acute care [2]. Further, research on outcomes after PDOC often fails to discriminate between diagnostic subtypes (UWS or MCS), aetiology and the time since injury [2]. Furthermore, data on quality of life, costs and cost-effectiveness of rehabilitation programmes, and caregiver burden are limited.

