#### Community integration questionnaire (CIQ)

The CIQ is a 15-item questionnaire that assesses participation in 3 domains: within the home environment, in social interactions, and in productive activities (work, school, or volunteering) [35]. The basis for scoring is primarily the frequency of performing activities or roles, with secondary weight given to whether activities are done jointly with others, and the nature of these other persons (for example, with/without TBI). CIQ scores range from 0 to 29, a higher total score indicates a higher level of participation.

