### Statistical analysis

Descriptive statistics will be used to present the outcomes of the study parameters and the socio-demographic data. Means and standard deviations will be calculated for variables on an interval scale and medians and interquartile ranges for ordinal variables. Proportions will be calculated for nominal variables.

Subgroup analyses will be performed for patients presenting in UWS versus MCS at baseline and for traumatic versus non-traumatic disorders of consciousness.

The proportions of patients transitioning from UWS to MCS and emergence from MCS to the conscious state will be calculated during and after EIN.

The course of recovery of consciousness (yes/no) over time will be analysed using Generalized Estimating Equations (GEE) analysis for logistic outcomes on an intention-to-treat basis. Assuming that data are missing at random, data imputation is unnecessary in GEE analysis; all observations are taken into account in contrast to complete case analyses. Recovery (yes/no) at each time point will be included as the dependent variable in the GEE model. Separate models will be generated for transitions from UWS to MCS and from MCS to the fully conscious state based on the CRS-R. Independent variables that will be added one by one to the models, include- measurement time (weeks), traumatic vs. non-traumatic aetiology, age at injury, and complications (yes/no or number). Significant predictors (*p* < 0.05) will be included in a multivariable model using a Bonferonni correction, dividing the significance level (alpha< 0.05) by the number of predictors included in the model.

Also using GEE analysis, the course of quality of life (EQ-5D-5L and Qolibri) and participation (CIQ) over time will be analysed using separate linear outcome models. The effects of time, cognitive (MoCa), behavioural (NPI), emotional (HADS), and motor status (FIM), and level of disability (DRS) and discomfort (NCS) on quality of life or participation during follow-up will be studied by adding these time-dependent variables (one by one) as independent variables to the models. Significant predictors (*p* < 0.05) will be added into a multivariable GEE-model to study the independence of these potential predictors on the outcomes using the Bonferroni correction.

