In caregivers, self-efficacy (GSES) and caregiver strain (CSI) are measured, which will also be modelled using GEE analyses. Independent variables added to these models include age and gender of the caregiver and the level of consciousness (UWS, MCS, or conscious), and the cognitive (MoCA) and motor (FIM) status of the patients.

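### The quality-of-life and participation models adjust for neither age nor aetiology, so the planned test of predictor independence cannot separate the status scores from either

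*Protocol article*

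**What the plan says.** All model specifications are in the Statistical analysis section of the protocol article.

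- **Quality of life and participation (EQ-5D-5L, QOLIBRI, CIQ).** The variables of interest are "The effects of time, cognitive (MoCa), behavioural (NPI), emotional (HADS), and motor status (FIM), and level of disability (DRS) and discomfort (NCS"). They "will be studied by adding these time-dependent variables (one by one) as independent variables to the models". Those with p < 0.05 enter a multivariable GEE model "to study the independence of these potential predictors on the outcomes using the Bonferroni correction". No baseline patient characteristic is listed.
- **Recovery of consciousness.** The candidates are "measurement time (weeks), traumatic vs. non-traumatic aetiology, age at injury, and complications (yes/no or number"). Age and aetiology are therefore on the list here.
- **Caregiver outcomes.** "Independent variables added to these models include age and gender of the caregiver", together with the patient's level of consciousness, MoCA and FIM.
- **Subgroups.** UWS versus MCS at baseline and traumatic versus non-traumatic are announced in general terms. There is no subgroup by age.

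Three other places bear on the point. The Background states: "Prognostic factors associated with better recovery from PDOC are younger age at onset, traumatic aetiology, less severe comorbidities and less severe neurological impairment". Table 1 sets a lower age limit of 16 years and no upper limit. The CIQ covers participation at home, "in social interactions, and in productive activities (work, school, or volunteering").

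**The concern.** Quality of life and participation are among the main outcomes named in the Background. The multivariable model is the step from which a score would be reported as an independent predictor of them.

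By the protocol's own account, younger and traumatic patients recover better, so age and aetiology plausibly influence MoCA, FIM and DRS. Age also plausibly influences the CIQ directly: a student and a retired person differ in work and schooling whatever their injury. A variable that affects both predictor and outcome and is left out of the model passes part of its effect to the predictor. GEE as planned has no patient-specific fixed effects, so age differences between patients feed into the score coefficients. A cognitive or motor effect on participation could then be partly an age effect and still be called independent.

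**Working it through.** **1. Covariate lists side by side**

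| Models | Baseline patient variables listed | Other variables listed |
|---|---|---|
| Recovery of consciousness | age at injury, aetiology | time, complications |
| EQ-5D-5L, QOLIBRI, CIQ | none | time, MoCA, NPI, HADS, FIM, DRS, NCS |
| Caregiver GSES, CSI | none | caregiver age and gender; patient level of consciousness, MoCA, FIM |

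The middle row has seven candidates. If all seven enter the multivariable model, the Bonferroni level is 0.05/7 = 0.0071. With fewer predictors it is less strict, for example 0.05/3 = 0.0167. The correction moves the threshold but does not remove bias in the coefficient.

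**2. Size of the bias in closed form**

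The protocol gives no correlation of age with any score or outcome, so these inputs are assumptions. Let the standardised outcome depend on age alone with slope g, and let a score with no effect of its own correlate r with age (signs chosen so that the product is positive). The spurious standardised slope is r × g. Treating patients as N independent units:

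- z = atanh(r × g) × √(N − 3)
- rejection rate = 1 − Φ(c − z) + Φ(−c − z), with c = 1.960 at 0.05 and c = 2.690 at 0.05/7

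N = 72 is the planned enrolment. N = 40 is an assumed number of assessable patients.

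| r = g | r × g | N = 72: z | at 0.05 | at 0.05/7 | N = 40: z | at 0.05 | at 0.05/7 |
|---|---|---|---|---|---|---|---|
| 0 | 0 | 0 | 5.0% | 0.7% | 0 | 5.0% | 0.7% |
| 0.2 | 0.04 | 0.332 | 6.3% | 1.0% | 0.243 | 5.7% | 0.9% |
| 0.3 | 0.09 | 0.750 | 11.6% | 2.6% | 0.549 | 8.5% | 1.7% |
| 0.4 | 0.16 | 1.341 | 26.8% | 8.9% | 0.982 | 16.6% | 4.4% |

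**3. Size under the planned type of model**

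Simulation of a linear GEE with exchangeable correlation and bias-reduced variance. Assumptions: 40 patients, 4 follow-up visits, within-patient correlation 0.6, and one time-dependent score with no effect of its own. Age correlates equally with score and outcome. Ranges are across repeat runs.

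| Age correlation (absolute) | at 0.05, age omitted | at 0.05, age included | at 0.05/7, age omitted |
|---|---|---|---|
| 0.3 | about 8% | 4–6% | 1–3% |
| 0.4 | 12–14% | 5–6% | about 3% |
| 0.5 | 23–26% | 5–7% | 8–9% |

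With a divisor of 3 and age omitted, the rates were about 5%, 7% and 12%.

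**4. Precision**

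The variance of the score coefficient is proportional to the residual outcome variance divided by the variance of the score given the other covariates. If age correlates ρ with both, adding age multiplies both by (1 − ρ²), and (1 − ρ²)/(1 − ρ²) = 1. The simulated mean standard errors without and with age agree with this: 0.0803 and 0.0809 at 0.3, 0.0815 and 0.0818 at 0.4, 0.0817 and 0.0821 at 0.5.

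**The case against.** **The analysis is exploratory, and a fuller plan may add covariates.** True. But the article does not leave the list open. It names the variables for these models and the purpose of the multivariable step, and the list does not serve that purpose if independence is to include independence from age.

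**Independence may mean only mutual independence of the listed scores.** This is a natural reading, and on it the model does what it says. The wording does not exclude the wider reading, though, and a clinical reader of the results is likely to take it that way.

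**Aetiology is partly covered.** The traumatic versus non-traumatic subgroup analysis is not restricted to any outcome. This stands in part: it would help if applied to these outcomes, but it is not tied to these models and does nothing about age.

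Four stronger readings are tempting, and the documents do not support them.

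- *That the effects are confounded by age.* No section gives an association of age with the CIQ, EQ-5D-5L or QOLIBRI. The inference rests on age being prognostic for recovery, on the open age range and on the content of the CIQ. It is weaker for quality of life than for participation.
- *That up to a quarter of null scores would be reported as independent predictors.* The 8% to 25% range applies at the 0.05 screening step. At 0.05/7 it is about 1% to 9%. The simulation also holds a single score; in the multivariable model the other scores could absorb part of an age effect.
- *That leaving age out costs power.* The usual gain from a prognostic covariate assumes that it is uncorrelated with the predictor, and then there is no confounding either. With equal correlations the gain is nil (step 4 of the working). Age is also constant within a patient, so it cannot sharpen the within-patient part of a time-dependent effect. The protocol states no power.
- *That these are the only models lacking baseline patient variables.* The caregiver models list none either, only the caregiver's own age and gender. The valid comparison is with the recovery models.

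**Conclusion.** The point holds as a limit on what the planned model can show. As written, it can establish independence of the status scores from one another, but not from age or aetiology. Effects on participation, and less certainly on quality of life, may be partly age effects. Neither the Bonferroni correction nor the announced subgroups remove this.

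The size cannot be fixed from the protocol. With assumed age correlations of 0.3 to 0.5 with both score and outcome, false positives for a null score run from about 8% to 25% at 0.05 and from about 1% to 9% at 0.05/7 (nominal 0.7%). At 0.3 the inflation is small, and if age and score are uncorrelated there is none. These figures also rest on the assumed 40 assessable patients, 4 visits and within-patient correlation of 0.6.

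**What to change.** In the Statistical analysis section, state that age at injury and aetiology (traumatic or non-traumatic) enter every EQ-5D-5L, QOLIBRI and CIQ model as prespecified adjusters, at both the one-by-one and the multivariable step, whatever their p-values. State also that they do not count in the Bonferroni divisor. With all seven candidates retained, the level then stays at 0.05/7 = 0.0071. If the two adjusters were counted it would fall to 0.05/9 = 0.0056.

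This goes further than the recovery models, where the same variables are candidates screened at p < 0.05. The difference is deliberate: here they are adjusters, and in a small cohort a confounder can fail a significance screen and still bias a coefficient.

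The cost is a sentence or two of wording and two extra parameters per model in a small cohort. No new data are needed, since both variables are already planned for the recovery models. No gain in precision or power should be claimed for the change.

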## Methods

### Study design and setting

The DOCTOR study is a nationwide single-centre prospective cohort study with 2 years follow-up. Measurements take place at start EIN, in week 5, 10, and at discharge of the EIN programme (duration = max 14 weeks) and at week 28, 40, 52, and 104 after admission to the EIN programme, following patients through the health-care chain. (Fig. 1).

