### EIN programme

The EIN programme is a subacute medical rehabilitation programme of 14 weeks (or less when recovery of consciousness occurs earlier) and meets the guideline recommendations for patients with PDOC published by the American Academy of Neurology [26]. An interdisciplinary rehabilitation team of a rehabilitation physician, a physician assistant, a neuropsychologist, cognitive rehabilitation therapists, physiotherapists, occupational therapists, speech therapists, nursing staff, dietician, and social worker uses an integrated approach in a 24/7 setting [19] with a minimum duration of 120 min therapy per day in which daily routines are built in together with a structured scheme of therapy and rest. The program is focused on optimizing the metabolic state, nourishment, respiration and skin condition, as well as diminishing the risk of infections and quick removal of invasive devices, like a tracheostomy tube or a urinary catheter, and recovery of the normal circadian cycle. Pharmacological treatments and structured stimulation of all sensory modalities (vision, hearing, smell, taste, touch, posture and motion, pain and temperature) aim to generate maximal arousal. As soon as the patient shows any voluntary reactions, reflecting a change from UWS into MCS, the focus of treatment changes from stimulation to training of cognitive functions. Motor rehabilitation aimed at optimising postural and motor activity helps restore bodily integrity and reduces the risk of complications (e.g., infection, thrombo-embolic complications, skin breakdown). For patients who reach MCS, increased time is spent on training mobility and self-care. Coping and self-efficacy of caregivers are addressed with psychoeducation, counselling and hands-on training in handling the patient.

After EIN, patients are discharged to 1) a regular neurorehabilitation setting in case of full recovery of consciousness and the ability to participate in a rehabilitation programme as judged by the rehabilitation physician, 2) to skilled nursing facilities, 3) sheltered housing or 4) possibly home (Fig. 2). Some skilled nursing facilities offer a prolonged intensive neurorehabilitation programme (PIN) for further recovery of consciousness during a period of up to 24 months post-injury. EIN is part of an academic network of expertise (EENnaComa) in which various healthcare institutes specialised in post-acute and long-term care of PDOC patients and their families are united.

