### Data collection

In 4 years we aim to include 72 patients. Structured data collection (Fig. 3) will take place at the start of the EIN programme at week 5, 10, and at EIN discharge (week 14). LOC assessment and registration of complications will be done weekly.

After discharge from EIN, follow-up measurements are planned at 28, 40, 52, and 104 weeks post-inclusion. These will take place at the patients’ actual health-care institution or residence.

All measurements conducted during the EIN programme are performed by trained members of the rehabilitation team. Follow-up measurements are performed by a trained research assistant.

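### The caregiver strain and self-efficacy models do not list measurement time, so any general trend in caregivers would be partly credited to the patient's recovery

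*Protocol article*

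**What the plan says.** The Statistical analysis section of the protocol article describes three families of GEE model and names covariates for each.

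- **Recovery of consciousness:** "Independent variables that will be added one by one to the models, include- measurement time (weeks", followed by aetiology, age at injury and complications.
- **Quality of life and participation:** "The effects of time, cognitive (MoCa), behavioural (NPI), emotional (HADS), and motor status (FIM", followed by disability (DRS) and discomfort (NCS).
- **Caregivers:** "In caregivers, self-efficacy (GSES) and caregiver strain (CSI) are measured, which will also be modelled using GEE analyses". The covariates are given as "Independent variables added to these models include age and gender of the caregiver and the level of consciousness (UWS, MCS, or conscious". The patient's MoCA and FIM complete the list.

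Time appears in the first two lists and not in the third. The Abstract classes caregiver self-efficacy and strain as secondary outcomes.

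**The concern.** Level of consciousness, MoCA and FIM vary over time, and in this cohort they are tied to time since admission. Table 1 admits only patients in UWS or MCS, so nobody counts as conscious at the start. The Discussion says that recovery of consciousness falls mostly in the first 1 to 1.5 years and functional recovery mostly by one year.

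Caregivers may have a course of their own over the same period. The EIN programme section says that caregivers are taught, counselled and trained in handling the patient, with coping and self-efficacy as the target. The programme is thus meant to move GSES during weeks in which some patients recover.

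Without time in the model, such a trend is partly absorbed by the patient-status coefficients. General adaptation could then be read as relief brought by the patient's recovery, and general exhaustion as burden brought by it. The article intends its results to improve the care chain for families as well as patients.

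**Working it through.** The article gives no effect size, SD or power for the caregiver outcomes, so it has no figure to reproduce. The check is whether the mechanism works at a size that matters.

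**Inputs from the article**
- Planned size: "In 4 years we aim to include 72 patients". One caregiver per patient is taken.
- Visits: start, weeks 5 and 10, discharge (at most week 14), then "at week 28, 40, 52, and 104 after admission to the EIN programme". The instrument schedule is in a figure that is not shown, so using all eight visits for caregivers is an assumption.
- CSI runs from 0 to 13, with higher scores meaning more burden.

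**Assumed inputs**
- CSI total SD of 3 and within-caregiver correlation of 0.5. The between- and within-caregiver SDs are then each 3 × √0.5 = 2.12.
- 30% or 60% of patients recover by week 104, with exponential recovery times of mean 26 weeks among those who recover.
- Drift D of 0, −1 or −2 CSI points over 104 weeks.
- No deaths and no missed visits.

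**Model.** For caregiver i at week t:

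CSI = 6 + D × f(t) + 0 × conscious + u_i + e_it

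The true effect of consciousness is zero. The drift has one of two shapes:
- linear: f(t) = t/104
- early plateau: f(t) = (1 − e^(−t/26)) / (1 − e^(−4)). At week 28 this is 0.659/0.982 = 0.67, so two thirds of the drift has occurred by then.

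Each data set was fitted by GEE (exchangeable correlation, robust standard errors) without time, with linear time, and with visit categories. There were 200 runs per scenario at 30% recovery and 150 at 60%. The Monte Carlo standard error of a rejection rate is at most √(0.25/150), about 4 percentage points.

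**Results:** mean consciousness coefficient (share of runs with p < 0.05)

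| Recovered | Drift | Shape | Without time | Linear time | Visit categories |
|---|---|---|---|---|---|
| 30% | 0 | – | 0.01 (7.5%) | 0.01 (7%) | 0.02 (6%) |
| 30% | −1 | linear | −0.44 (28%) | −0.04 (7.5%) | −0.04 (6%) |
| 30% | −1 | plateau | −0.48 (29%) | −0.11 (10.5%) | 0.03 (8%) |
| 30% | −2 | linear | −0.83 (67.5%) | 0.00 (10%) | −0.01 (8%) |
| 30% | −2 | plateau | −0.99 (83.5%) | −0.22 (9.5%) | 0.04 (6.5%) |
| 60% | 0 | – | −0.01 (6%) | −0.02 (8%) | −0.01 (5.3%) |
| 60% | −1 | linear | −0.45 (49.3%) | −0.03 (2%) | −0.02 (2.7%) |
| 60% | −1 | plateau | −0.54 (60.7%) | −0.16 (8%) | −0.01 (4.7%) |
| 60% | −2 | linear | −0.86 (95.3%) | −0.01 (4.7%) | 0.00 (4.7%) |
| 60% | −2 | plateau | −1.07 (96.7%) | −0.32 (19.3%) | −0.02 (8%) |

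**Share of drift transferred without time** = coefficient / drift. The lowest is 0.827/2 = 41% and the highest is 0.537/1 = 54%.

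A separate simulation used SDs of 2 between and within caregivers, half of patients recovering (mean about 27 weeks) and drift in both directions. Without time, a drift of 1 point gave a false effect of 0.43 to 0.45 points (significant in 44 to 45% of 300 runs). A drift of 2 points gave 0.86 points (92 to 93%). The sign followed the drift.

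**Not covered:** GSES was not simulated. MoCA and FIM were not in the simulated model; with them included, the absorbed drift could be spread over several coefficients.

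**The case against.** **The list is open.** The covariates are introduced by the verb *include*, and the caregiver outcomes are said to be modelled *also* by GEE, straight after models of course over time. A fuller plan may contain time. This stands: a reader might infer that time is excluded and that a false recovery effect will be reported, but the article says neither. The gap is still more than missing detail. The article names covariates family by family, and only the caregiver list lacks time.

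**Drift is not shown to exist.** This also stands. Nothing in the article gives a size for a trend in CSI or GSES, and with no drift the model without time rejects at only 6 to 7.5%. A wrong-signed effect is not demonstrated either, because the true effect was set to zero throughout.

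**The other models do not protect time.** One might say that the article already forces time into its patient models and should do the same here. It does not: time is one of the variables entered one by one, and only predictors with p < 0.05 go forward. Those models are a precedent for naming time, not for retaining it.

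**Residence.** A reader might infer that the patient's residence is a second omission. The article does not support that. Residence is in none of its models. Of the discharge destinations, only regular neurorehabilitation is tied to full recovery of consciousness; the others, "2) to skilled nursing facilities, 3) sheltered housing or 4) possibly home", carry no such condition. Destination also follows partly from recovery, so residence may lie on the path from recovery to strain, and adjusting for it could remove part of the effect of interest.

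**Stakes.** The outcomes are secondary, the study is observational, and the text makes no causal claim about recovery and caregivers. This limits the weight of the point but does not remove it.

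**Conclusion.** The point holds as a conditional one. If the caregiver models are fitted with only the listed covariates, any general trend in strain or self-efficacy will be partly attributed to the patient's state. For CSI, under assumed drifts of 1 to 2 points over two years, that means a false consciousness effect of about 0.4 to 1.1 points, or 40 to 55% of the drift. The size rests on the assumed drift, SDs, recovery rates and visit schedule. The direction of the mechanism rests on the article's own account of who is enrolled and when they recover.

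**What to change.** State that measurement time is in every GSES and CSI model from the start, before caregiver and patient variables are added, and that it stays there whatever its p-value. Visit categories are preferable. They brought the coefficient to within 0.04 of zero in every scenario, with rejection of 3 to 8%. A linear term left a bias of 0.11 to 0.32 points, with rejection of 8 to 19%, when the drift came early and levelled off.

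No new data are needed, because the visit week is already recorded. The cost is somewhat wider intervals for level of consciousness, MoCA and FIM, and a few more parameters when time is categorical. No adjustment for residence is asked for.
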